### 2.5. Randomization

Eligible patients will be randomly assigned, in a 1:1 ratio, to the treatment group or the control group by means of a central web-based randomization tool. Random numbers will be generated by an independent data statistician using SAS 9.3 software (SAS Institute, Cary, NC). The researcher will enter the patient information on the computer and will be assigned a random number based on which the grouping will be completed. Efficacy assessors will be unaware of the study-group protocol, and data statisticians have no role in the design or conduct of the study.

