#### 2.3..2. Inclusion criteria.

(1) Meet the diagnostic criteria of type 2 DKD;(2) Age ≥ 18 years old and ≤ 70 years old, regardless of gender;(3) With the 24-hour urinary protein quantification was 0.5 to 3.5 g;(4) With serum creatinine < 265μmol/L (3 mg/dL);(5) Patients voluntarily participated in the trial and signed informed consent.

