### 2.4. Sample size

The sample size of this study was calculated based on the change in 24-hour urinary protein quantification (the difference in the standard deviation of the mean value of 24-hour urinary protein quantification before and after treatment) after 12 weeks of treatment, which was 0.87 ± 0.41 in the treatment group according to the results of the pilot study, and the control group was 0.65 ± 0.33. PASS15.0 software was used to estimate the sample size and set α = 0.05, β = 0.10. Finally, 37 participants are needed in each group, and the dropout rate was estimated to be 10%. The total required sample size will be 84 cases, 42 cases in each group.

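### No stratification factor is named and the stated one-way ANOVA does not adjust for baseline urinary protein, so a chance baseline gap stays in the primary estimate

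*Protocol article*

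**What the plan says.** Section 2.5 states: "Eligible patients will be randomly assigned, in a 1:1 ratio, to the treatment group or the control group by means of a central web-based randomization". On the list it says "Random numbers will be generated by an independent data statistician using SAS 9.3 software", and on the assignment step that the patient "will be assigned a random number based on which the grouping will be completed". Blocks, strata and minimisation are not mentioned, either as used or as not used.

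Section 2.4 sizes the trial on change in 24-hour urinary protein over 12 weeks: "0.87 ± 0.41 in the treatment group according to the results of the pilot study", while "the control group was 0.65 ± 0.33". The planned difference is therefore 0.87 − 0.65 = 0.22 g. The section continues "37 participants are needed in each group" and, after 10% dropout, "The total required sample size will be 84 cases, 42 cases in each group".

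Inclusion criterion 3 (section 2.3.2) reads "With the 24-hour urinary protein quantification was 0.5 to 3.5 g". Section 2.7.1 lists the primary outcome as the protein value at baseline and four later visits. Section 2.9 names one-way ANOVA for normally distributed measurements between groups, and a Wilcoxon rank sum test for skewed ones. Neither takes account of baseline.

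**The concern.** The primary variable is known in every patient before allocation, and the entry range is seven-fold (3.5/0.5). With 84 patients, chance alone can leave the arms visibly apart on it. Two devices usually deal with this: stratified allocation beforehand and baseline adjustment afterwards. The article names no factor for the first, and the test it names leaves out the second.

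At stake are precision and credibility. If one arm starts 0.2 g or more higher, a reader cannot easily separate the treatment effect from the head start in an unadjusted comparison. Across all possible allocations, the same variation widens the confidence interval.

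**Working it through.** **The plan's own figures.** The dropout step reproduces: 37/0.9 = 41.1, rounded up to 42. The 37 does not. With mean variance (0.41² + 0.33²)/2 = 0.1385, n per arm = 2 × 0.1385 × (1.960 + 1.282)²/0.22² = 60.2, so 61 for a two-sided 5% test at 90% power; one-sided it is 50. That is a separate and larger problem. It matters here only because the power figures below are recomputed from the pilot values.

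**Arm sizes, if allocation were simple.** Binomial(84, 0.5) gives exactly 42:42 with probability 8.7%, and 48:36 or worse with probability 23%. The cost in power is small:
- At 42:42, SE = √((0.41² + 0.33²)/42) = 0.0812, and two-sided power = Φ(0.22/0.0812 − 1.96) = 77.3%.
- Averaged over all random splits, power is 76.8%, a loss of about 0.5 points.
- At 48:36 it is 75.2% or 77.7%, depending on which arm is larger.

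**Baseline gap without stratification.** At 42 per arm, the SE of the difference in baseline means is SD × √(2/42) = 0.218 × SD. The article gives no baseline SD. A uniform spread over 0.5 to 3.5 g would give 3.0/√12 = 0.87 g, and 0.5 to 1.0 g is taken as the range.

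| Assumed SD (g) | SE of gap (g) | 0.22/SE | P(gap > 0.22 g) at 42:42 | Averaged over random splits |
|---|---|---|---|---|
| 0.5 | 0.109 | 2.02 | 4.4% | 4.5% |
| 0.7 | 0.153 | 1.44 | 15.0% | 15.2% |
| 0.87 | 0.189 | 1.16 | 24.4% | 24.7% |
| 1.0 | 0.218 | 1.01 | 31.3% | 31.6% |

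The last two columns hardly differ, so blocking alone does nothing for baseline balance.

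**How much of the gap reaches the estimate.** Let b be the slope of week-12 protein on baseline. A gap g adds b × g to the difference in week-12 level and (1 − b) × g to the difference in fall from baseline. For example, b = 0.7 and g = 0.22 g give 0.154 g on level and 0.066 g on change.

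**Size in terms of variance.** Simulated SD of the treatment estimate (6,000 trials), assuming each patient's protein falls in proportion to baseline, and baseline is uniform or a log-normal truncated to the entry range (SD 0.70 g):

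| Analysis | Uniform: simple → stratified | Log-normal: simple → stratified |
|---|---|---|
| Week-12 level, unadjusted | 0.179 → 0.137 | 0.142 → 0.113 |
| Change, unadjusted | 0.132 → 0.122 | 0.105 → 0.098 |
| Baseline-adjusted | 0.121 → 0.118 | 0.094 → 0.093 |

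- Adjustment alone (first entries in each column): against level, 1 − 0.121/0.179 = 32% and 1 − 0.094/0.142 = 34%; against change, 8% and 10%.
- Stratification without adjustment: 20% to 23% on level, 6% to 8% on change.
- Stratification on top of adjustment: 1.1% and 2.5% on these rounded values, so about 2% at most.

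These simulated SDs serve as ratios only. The value 0.132 implies a patient-level change SD of 0.132/0.218 = 0.61 g, above the pilot's √0.1385 = 0.37 g.

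**Effect of stratifying.** With two strata, blocks of 4 and a uniform baseline, simulation brings the chance of a gap above 0.22 g from about 25% to about 5% with a 1.5 g cut, and to about 2% (2.3% to 2.7% across runs) with a 2.0 g cut.

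**The case against.** A reader might infer that allocation is simple, with no blocks and no strata, so that 42 per group will usually not be met and the allocation method is itself flawed. The article does not support this. The sentence on the random number describes how a patient receives a number, not how the list was built. A permuted-block list made in SAS would fit that sentence, the 1:1 ratio and the planned 42 per group. A condensed article may leave block and strata details to the full protocol. Even if allocation were simple, uneven arms cost about half a point of power on average.

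A reader might also take a 0.22 g baseline gap as cancelling or mimicking the planned effect. That is too strong. The 0.22 g is a difference in change, and only the fractions shown above carry over. Chance imbalance under valid randomisation is not bias, and the test's error rate already allows for it. Unstratified central allocation is a legitimate design.

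Finally, an unseen analysis plan might adjust for baseline. That possibility stays open, but section 2.9 is not merely silent: it names a between-group test, and that test has no baseline term. This part of the concern stands, as does the absence of any named stratification factor.

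**Conclusion.** The point holds as one of avoidable imprecision, mainly in the analysis and secondarily in the allocation. Under unstratified allocation, a baseline gap above 0.22 g arises in about 4% to 32% of trials for an assumed SD of 0.5 to 1.0 g, and the stated ANOVA leaves its effect in the estimate. Under proportional falls, adjusting for baseline cuts the SD of the estimate by about a third if level is compared and by 8% to 10% if change is compared. Section 2.4 is written in terms of change and section 2.7.1 in terms of the value at each visit, so either comparison is possible. These sizes rest on assumed baseline distributions, because the article gives no baseline SD. Whether the list is blocked or stratified cannot be settled from the article.

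**What to change.** 1. In section 2.9, replace the one-way ANOVA for the primary outcome with a linear model (ANCOVA) of week-12 24-hour urinary protein on group and continuous baseline value. This costs one sentence and uses data already collected.
2. In section 2.5, state whether the list is blocked or stratified. If it already is, saying so closes this part.
3. If it is not, set the web tool to permuted blocks stratified by baseline protein, with a cut near the middle of the expected distribution, and keep the baseline value or stratum in the model. This is one setting and must be made before recruitment. The baseline urine result must be available before allocation, which criterion 3 already requires.

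Step 1 brings most of the gain. Step 3 mainly improves visible balance. It does not guarantee exactly 42:42: blocks of 4 in two strata gave an exact split in about 62% of simulated trials, though in simulation the smaller arm did not fall below 40.

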### 2.6. Interventions

Basic treatment: treatment protocols will be developed based on the basic treatment principles established by the *2012 American Diabetes Association Practice Guidelines*,^[7,17]^ as follows: provision of health education, such as diet and exercise guidance; glycemic control; biguanides will be used in patients with obesity and/or eGFR higher than 60 mL/min/1.73 m^2^; nonobese patients and/or patients with eGFR below 60 mL/min/1.73 m^2^ will receive glinide drugs. When blood glucose control is not ideal, choose 2 oral drugs or insulin supplementation. Hemoglobin A1c (HbA1c) will be controlled below 9.0%; blood pressure control: angiotensin-converting enzyme inhibitors/angiotensin receptor blockers will be recommended. For patients whose blood pressure cannot be controlled to 140/90 mm Hg with angiotensin-converting enzyme inhibitors/angiotensin-receptor blockers, nondihydropyridine calcium channel blockers will be added, and diuretics and/or beta blockers will be added. Blood pressure will be controlled to 140/90 mm Hg or less in all patients; blood lipid control: select statins or fibrates based on blood lipid of patients.

Warm acupuncture treatment: patients will be in a sitting position, and 75% alcohol will be used to disinfected the acupuncture site. The acupuncture points are Shenshu (BL 23), Sanyinjiao (SP 6), Taixi (KI 3), Xuehai (SP 10), Pishu (BL 20), Zusanli (ST 36) and Guanyuan (CV 4), acupoint positioning is based on the positioning standards in the *National Standards of the People’s Republic of China*.^[18]^ Disposable stainless steel acupuncture needles (0.25mm × 40mm, Suzhou Hualun Medical Appliance Co., Ltd, Suzhou, China) will be used and operated by an acupuncture-moxibustion practitioner with 3 years of clinical experience. After arrival of qi, a 27-mm piece of moxa stick (Nanyang Baicaotang Co., Ltd, China, size: 18 mm × 27 mm) will be added to the handle of the needle. The bottom of the moxa stick is about 20 mm away from the skin, and the pad is separated by a small piece of paper. The bottom of the moxa section will be ignited, and the treatment will be finished after the moxa sticks was burned out. The treatment will be given for 30 minutes each time, once every other day.

The patients in the treatment group will receive basic treatment combined with warm acupuncture, while the patients in the control group only receive basic treatment. Both groups will continue to receive standard treatment for 12 weeks.

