## 2. Materials and methods

### 2.1. Study design

This is a prospective randomized controlled trial to investigate the efficacy and safety of warm acupuncture in the treatment of type 2 DKD. The patients who meet the criteria will be randomly divided into the treatment group and the control group. According to the recommendations of clinical guidelines, the 2 groups of patients will be treated with conventional Western medicine, and the treatment group will be treated with warm acupuncture in addition, follow up for 24 weeks after 12 weeks of continuous treatment. Flow diagram is shown in Fig. 1, and study schedule is shown in Table 1. This experiment will follow the Standards for Reporting Interventions in Clinical Trials of Acupuncture^[13]^ and the comprehensive trial report standard.^[14]^ The study will be completed under the guidance of Standard Protocol Items: Recommendations for Interventional Trials (SPIRIT checklist) 2013 statement.

**Table 1 T1:** Study schedule.

Stage project	Screening period	Treatment period		Follow-up	
	Baseline	8 wk	12 wk	12 wk	24 wk
Record fill	√				
Fulfill inclusion criteria and exclusion criteria	√				
Sign informed consent	√				
Random allocation	√				
Treatment	√	√	√		
Effectiveness observation					
24-hr urinary protein quantification	√	√	√	√	√
Kidney function	√	√	√		√
The TCM Syndrome score	√	√	√		√
Safety assessments					
Routine blood tests	√	√	√		√
Blood test and urinalysis	√	√	√		√
Liver function	√	√	√		√
Electrocardiographic	√	√	√		
Record of adverse event		√	√	√	√

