## 3. Discussion

DKD is a serious microvascular complication, which is caused by long-term diabetes or poor blood glucose control, and is also an important factor in the death of diabetic patients.^[19]^ The pathogenesis of DKD is complex, and the early symptoms are occult. Therefore, clinical attention should be paid to the treatment and control of DKD.^[20]^

The pathogenesis of DKD is complicated. In recent years, the theory of autophagy has been widely used in the study of metabolic diseases, and it has been found that it is closely related to the damage of target organs. Autophagy is an important life phenomenon of living organisms; however, if autophagy is abnormally activated due to environmental stress and other factors, its autophagy expression beyond a certain physiological range will in turn cause damage to target cells, thus causing damage to target organs. The occurrence of diabetic kidney damage is closely related to the abnormal activity of autophagy and directly related to the degree of urinary protein.^[15]^ Western medicine treatment is mainly aimed to control the risk factors and further control the progress of the disease, but the clinical efficacy is still not satisfied.^[21]^

Studies have confirmed that the bidirectional regulation of acupuncture and moxibustion has something in common with the bidirectional regulation of autophagy expression. Acupuncture and moxibustion can effectively reduce urinary microprotein excretion, alleviate kidney injury and improve renal function in patients with early DKD.^[21,22]^ Warm acupuncture is a further development of acupuncture, clinical studies have shown which can reduce blood viscosity, improve microcirculation, regulate immune function, and inhibit platelet aggregation.^[23]^ Although evidence has shown that warm acupuncture is beneficial for patients with DKD, whether it can be used as a complementary or alternative treatment regimen for DKD remains controversial. We will use this study to investigate the clinical efficacy of warm acupuncture in the treatment of DKD, which is beneficial for both patients and clinical decision makers.

There are also some shortcomings in this study: due to the factors of treatment methods, this study could not achieve double blindness, which may have some impact on the study results; at the same time, there may be population regionalization in the study.

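### Background drugs can be changed after open allocation, with no stable regimen required at baseline, no named measurement of the stated targets in Table 1, and an unadjusted primary comparison

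*Protocol article*

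**What the plan says.** **Background treatment (section 2.6).** ACE inhibitors or ARBs are recommended. Where they do not bring blood pressure to 140/90, "nondihydropyridine calcium channel blockers will be added, and diuretics and/or beta blockers will be added". The target is common to both arms: "Blood pressure will be controlled to 140/90 mm Hg or less in all patients". Glucose-lowering treatment is extended to two oral drugs or insulin when control is judged inadequate, a term the section does not define; the HbA1c target is below 9.0%. Statins or fibrates are chosen from the patient's lipids. Control patients receive this treatment alone.

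**Eligibility (sections 2.3.2 and 2.3.3).** Urinary protein must lie between 0.5 and 3.5 g. No criterion concerns the stability of background drugs, and Table 1 shows one baseline visit with no run-in.

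**Blinding (section 2.5 and Discussion).** Efficacy assessors are blinded. The Discussion concedes that "due to the factors of treatment methods, this study could not achieve double blindness".

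**Measurements (Table 1 and section 2.7).** The primary outcome, "24-hr urinary protein quantification", is scheduled at all five time points. Kidney function, the TCM score, blood tests, urinalysis, liver function, ECG and adverse events also have rows. Blood pressure, HbA1c, lipids and concomitant drugs are not named.

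**Analysis and planning values (sections 2.9 and 2.4).** The between-group comparison is a one-way analysis of variance or a rank test, with no covariate stated. The pilot changes in urinary protein were "0.87 ± 0.41 in the treatment group according to the results of the pilot study, and the control group was 0.65 ± 0.33".

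**The concern.** The question of interest is what warm acupuncture adds to basic treatment. That contrast is clean only if basic treatment is delivered alike in both arms. Here it may be started or changed at or after randomisation, inside the 12 weeks over which the primary outcome is expected to move, in a trial where the arm is visible to patients and to whoever gives the needling. If drugs are stepped up more often in one arm because the arm is known, randomisation gives no protection and the difference in urinary protein mixes two causes. More step-up in the acupuncture arm would look like an acupuncture effect; more in the control arm would hide one.

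The stated analysis has no term for background treatment at baseline. The named schedule also gives no means of showing that the section 2.6 targets were met or that the arms were treated alike.

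**Working it through.** **The texts side by side.** Section 2.6 sets targets for blood pressure and HbA1c and bases drug choice on lipids. Table 1, presented as the study schedule, itemises measurements down to the ECG but has no row naming any of these three, nor the drugs themselves. The elimination criteria (section 2.3.4) remove patients whose regimen must change because of rapid progression; routine step-up under section 2.6 is not covered.

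**Inputs from section 2.4.** Change 0.87 (SD 0.41) with acupuncture and 0.65 (SD 0.33) in control; 37 per group, 42 after 10% dropout; α = 0.05, β = 0.10. No unit or direction is given. I read the changes as falls in g per 24 hours, following the unit in section 2.3.2, and the pilot control arm as having had basic treatment alone.

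**The plan's own figures.** The dropout step reproduces: 37/0.9 = 41.1, rounded up to 42. The 37 does not. The common SD is √((0.41² + 0.33²)/2) = 0.372, and two-sided α = 0.05 with 90% power needs 61 (normal) or 62 (t) per group. The 37 matches one-sided α = 0.05 with 80% power. That is a separate matter; 37 is used below only to obtain a standard error.

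**Size of the background change against the planned effect.**
- Planned difference: 0.87 − 0.65 = 0.22.
- Background change relative to it: 0.65/0.22 = 2.95, about three times.
- Relative difference in background response that equals the planned effect: 0.22/0.65 = 34%.
- Standard error of the difference at 37 per group: 0.372 × √(2/37) = 0.0865.
- Smallest significant difference: 1.96 × 0.0865 = 0.17, which is 26% of 0.65.

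**Illustration of bias (assumed inputs, not in the documents).** Suppose there is no acupuncture effect, a net excess share f of acupuncture-arm patients is stepped up after allocation, and each has an extra fall e. Then bias b = f × e, and the two-sided rejection rate is Φ(b/SE − 1.96) + Φ(−b/SE − 1.96).

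| f | e (g) | b (g) | b/0.22 | rejection rate |
|---|---|---|---|---|
| 10% | 0.2 | 0.02 | 9% | 5.6% |
| 20% | 0.4 | 0.08 | 36% | 15% |
| 30% | 0.6 | 0.18 | 82% | 55% |

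With the excess in the control arm, the sign of b reverses.

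**Chance imbalance at baseline.** If 40% of patients newly start an ACE inhibitor or ARB (assumed), the standard error of the between-arm difference in that share at 42 per arm is √(2 × 0.4 × 0.6/42) = 0.107. With an assumed extra fall of 0.3 to 0.6 g per starter, one standard error corresponds to 0.03 to 0.06 g. This is random variation that the test's type I error already covers. It costs precision, and a baseline covariate can recover some of that.

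**The case against.** The strongest reply is that this is a journal article. A drug log, vital signs and the timing of prescribing decisions usually sit in the full protocol or case report form, and section 2.8 refers to a case report form that is not shown. The unspecified blood-test row and the baseline record row could hold HbA1c, lipids or drug history, and section 2.6 cannot be applied without measuring them. A reader might infer that these items are not recorded at all; the article supports only that Table 1 does not name them. What stands is that the stated targets and the schedule do not match, and that neither the eligibility criteria nor the stated analysis deals with background treatment.

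Other stronger readings also go beyond the text:

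- **That unblinded staff adjust the drugs.** The article does not say who adjusts them. It is a reasonable inference from assessor-only blinding and a control arm without sham, but it is not stated.
- **That alternate-day acupuncture sessions give more occasions to change drugs.** Table 1 is an assessment schedule and does not exclude other care visits for controls. The acupuncture practitioner is given no prescribing role.
- **That chance imbalance in drug starts is bias.** Under randomisation it is imprecision. Only differential adjustment after allocation is bias.

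It is also fair to say that both arms follow one algorithm with common targets and that the Discussion discloses the lack of blinding. That reduces the risk. It does not remove it, because the algorithm leaves discretion.

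Finally, the 0.65 may partly reflect diet and exercise guidance, or regression to the mean after selection on urinary protein, and the article does not itself state that the named drugs lower urinary protein. This limits the 34% figure to an indication of scale.

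**Conclusion.** The concern holds in this form: adjustable background treatment, no stable regimen required before baseline, open treatment with assessor-only blinding, and an unadjusted comparison together leave the primary result open to differential background adjustment after allocation. The direction is unknown; a reader might infer that it favours acupuncture, but nothing in the article fixes the sign.

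The scale that rests on the article alone is that the pilot control change is about three times the planned difference, so a background response differing by 34% would equal the planned effect, and one differing by about 26% would reach significance at 37 per group. This takes the 0.65 as a fall on basic treatment; the share due to drugs is unknown. The bias and rejection rates in the table depend on assumed inputs and run from negligible (5.6%) to serious (55%), so they show what is possible and do not estimate what will happen. The change is worth making because it is cheap. The finding does not show that the trial will be biased, and it judges no drug, dose or target.

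**What to change.** 1. Enter each patient's planned background regimen in the web randomisation system before the allocation is revealed.
2. Record baseline ACE inhibitor/ARB status (established and unchanged, or newly started/changed). Prespecify it, with baseline urinary protein, as a covariate in the primary comparison; ACE inhibitor/ARB status could instead be a stratification factor.
3. Name blood pressure, HbA1c, lipids and a concomitant-drug log in Table 1 at the existing visits, and report them descriptively by arm, so that section 2.6 and the study schedule are reconciled. If the full protocol already collects them, it is enough to say so.

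Keep the post-randomisation drug data descriptive: an analysis split by drug change would condition on something that allocation may have affected and could introduce bias of its own. None of this restricts clinically needed changes.

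The cost is a protocol amendment, a few data fields, HbA1c and lipid assays and blood pressure readings at visits where most patients already give blood, and possibly a slight delay before randomisation.
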